# Effect of a soft exosuit on daily life gait performance in people with incomplete spinal cord injury: study protocol for a randomized controlled trial

**DOI:** 10.1186/s13063-024-08412-2

**Published:** 2024-09-06

**Keywords:** Incomplete spinal cord injury, Exosuit, Gait, Ambulation, Home and community setting

## Abstract

**Background:**

People with incomplete spinal cord injury (iSCI) often have gait impairments that negatively affect daily life gait performance (i.e., ambulation in the home and community setting) and quality of life. They may benefit from light-weight lower extremity exosuits that assist in walking, such as the Myosuit (MyoSwiss AG, Zurich, Switzerland). A previous pilot study showed that participants with various gait disorders increased their gait speed with the Myosuit in a standardized environment. However, the effect of a soft exosuit on daily life gait performance in people with iSCI has not yet been evaluated.

**Objective:**

The primary study objective is to test the effect of a soft exosuit (Myosuit) on daily life gait performance in people with iSCI. Second, the effect of Myosuit use on gait capacity and the usability of the Myosuit in the home and community setting will be investigated. Finally, short-term impact on both costs and effects will be evaluated.

**Methods:**

This is a two-armed, open label, randomized controlled trial (RCT). Participants will be randomized (1:1) to the intervention group (receiving the Myosuit program) or control group (initially receiving the conventional program). Thirty-four people with chronic iSCI will be included. The Myosuit program consists of five gait training sessions with the Myosuit at the Sint Maartenskliniek. Thereafter, participants will have access to the Myosuit for home use during 6 weeks. The conventional program consists of four gait training sessions, followed by a 6-week home period. After completing the conventional program, participants in the control group will subsequently receive the Myosuit program. The primary outcome is walking time per day as assessed with an activity monitor at baseline and during the first, third, and sixth week of the home periods. Secondary outcomes are gait capacity (10MWT, 6MWT, and SCI-FAP), usability (D-SUS and D-QUEST questionnaires), and costs and effects (EQ-5D-5L).

**Discussion:**

This is the first RCT to investigate the effect of the Myosuit on daily life gait performance in people with iSCI.

**Trial registration:**

Clinicaltrials.gov NCT05605912. Registered on November 2, 2022.

**Supplementary Information:**

The online version contains supplementary material available at 10.1186/s13063-024-08412-2.

## Introduction

### Background/rationale

An incomplete spinal cord injury (iSCI) is caused by partial damage to the spinal cord and can lead to loss of motor, sensory, and autonomic functions, depending on the spinal level and severity of the lesion [1]. An iSCI can be caused by trauma, inflammation, vascular damage, or a neoplastic or degenerative process [1]. The estimated prevalence is 223–755 per million people worldwide [2, 3] with approximately 8000 people in the Netherlands [4]. People with iSCI often have decreased gait capacity, which limits their ability to ambulate in the home and community setting [5–7]. According to the World Health Organization’s International Classification of Functioning [8], gait capacity refers to what people are able to do in a standardized environment and daily life gait performance refers to what people habitually do in daily life (i.e., in the home and community setting). As a consequence of decreased gait capacity, people with iSCI are at risk of developing a sedentary lifestyle resulting in a vicious circle of declining daily life gait performance and gait capacity. Furthermore, a sedentary lifestyle increases the risk of secondary complications such as cardiovascular disease [9], muscle contractures [10], pressure sores [10], depression [11], chronic pain [11], and bowel problems [12]. This, in turn, puts them at an even higher risk to become inactive [13]. Conversely, increased gait capacity and daily life gait performance are related to improved health, more independence, better participation to society, and increased quality of life [14, 15].

To enhance ambulation in the home and community setting for people with spinal cord injury (SCI), assistive technology presents a compelling solution. Among the available options, powered assistive devices such as wearable exoskeletons offer significant potential. These devices use rigid structures to compensate for the loss of leg muscle strength [16] and are specifically designed for people with complete spinal cord injury who are otherwise wheelchair bound [17]. However, exoskeletons have notable limitations, e.g., their heavy weight (ranging from 13 to 48 kg) and their limited walking speed (0.1 m/s to 0.4 m/s) [18, 19]. Moreover, most exoskeletons completely take over the control of the lower limbs, irrespective of the contribution from active leg muscles [18]. Consequently, rigid exoskeletons are not well suited for people with iSCI who possess residual leg muscle strength and gait capacity.

A new breed of devices, known as soft exosuits, has been developed to assist neurological patients with residual leg muscle strength and gait capacity during walking [18]. A soft exosuit transmits forces across the lower-limb joints and consists of soft textiles with a minimum of rigid structures, making it light-weighted, but it requires substantial voluntary contribution from active leg muscles [20]. Exosuit designs vary from unilateral to bilateral and deliver mechanical support in different ways, e.g., ankle plantarflexion, knee extension, and/or hip extension [18, 21, 22]. One type of exosuit is the Myosuit, a commercially available bilateral exosuit providing assistance to knee and hip extension [23]. A pilot study involving participants with various neurological disorders has shown an increased gait speed while using the Myosuit compared to baseline gait speed measured in a standardized environment [18]. This study also showed that five training sessions of 45 min each was safe and feasible. There was a relatively high adherence to the study protocol and no adverse events were reported [18]. In addition, a case study with a person with iSCI has shown an increase in walking speed and walking efficiency with the Myosuit [24].

Currently, exoskeletons and exosuits are mainly used as gait re-training devices. Only one study showed that the Myosuit is feasible to be used for various activities in the home and community setting by people with leg muscle weakness [25]. However, to improve ambulation in the home and community setting in people with iSCI, the assistive effect of a soft exosuit on daily life gait performance needs to be investigated.

### Objectives

The primary study objective is to examine the assistive effect of a soft exosuit (Myosuit) on daily life gait performance in people with iSCI. The second objective is to investigate the effect of Myosuit use on gait capacity and the usability of the Myosuit in the home and community setting. Finally, short-term impact on both costs and effects will be evaluated. It is hypothesized that the assistive effect of the Myosuit increases daily life gait performance and that Myosuit use increases gait capacity in people with iSCI. It is also expected that its usability is satisfactory.

## Methods

### Regulation statement and ethics approval

The study is approved by the internal review board of the Sint Maartenskliniek and the regional medical ethics committee Oost-Nederland (2022–13719, NL80641.091.22). Any modifications of the protocol will be notified via an amendment. The trial has been registered on Clinicaltrials.gov (NCT05605912). This study will be conducted in accordance with the Declaration of Helsinki (64th WMA General Assembly, Fortaleza, Brazil, October 2013) and the Medical Research Involving Human Subjects Act. This protocol is reported according to the SPIRIT guidelines rand checklist [26]. All items of the WHO Trial Registration Data Set can be found in the protocol [27].

### Study design and setting

This study is conducted at the Sint Maartenskliniek within the Gait Expertise Center, Nijmegen, The Netherlands. When the inclusion of participants is insufficient, the possibility of including another rehabilitation center will be considered. A patient representative was involved during the design phase of the study. It is a single-center, two-armed, open-label randomized controlled trial (RCT) which is visualized in Fig. 1. For this study, a superiority framework is used. To achieve a valid evaluation of the effect of the Myosuit on daily life gait performance, a control group is added to the study design to control for bias due to non-specific effects of attention and training in the intervention group.

### Recruitment

Potential participants who meet the eligibility criteria will be recruited by rehabilitation physicians working in the outpatient clinic at the Sint Maartenskliniek. Alternatively, interested patients may apply for the study themselves by contacting one of the rehabilitation physicians or the researchers. All individuals expressing interest in the study and granting permission to share their contact details will be contacted by the primary researcher (LV), who will send the information letter. After 1 week, the primary researcher will follow-up with the patients to address any questions or concerns they may have regarding the information provided. If patients indicate that they are willing to participate, the primary researcher will verify their eligibility. In the case a patient has applied him/herself, his/her eligibility will be verified by one of the rehabilitation physicians as well. The primary researcher (LV) will obtain informed consent at the baseline visit. Participants can leave the study at any time for any reason if they wish to do so without any consequences.

### Eligibility criteria

#### Inclusion criteria

Participants must meet all of the following inclusion criteria:Spinal cord injury grade C or D according to the American Spinal Injury Association (ASIA) impairment scale,At least 6 months after injury,Age ≥ 18 years,Sufficient hand function to don and doff the Myosuit or having a caregiver who is available to help donning and doffing the Myosuit at home,Reduced gait capacity due to reduced knee and/or hip strength (Medical Research Council (MRC) scale < 5),Able to stand up from a chair without deviating to the left or right side more than 45° during the rising movement,Able to independently ambulate for 10 m with or without assistive devices,Having a personal aim to improve walking distance, speed, or gait capacity otherwise.

#### Exclusion criteria

If participants meet any of the following criteria, they will not be eligible:Another (neurological) disease that may influence motor performance,Wounds that can be worsened by wearing the Myosuit,Body height < 150 cm or > 195 cm,Body weight < 45 kg or > 110 kg,Pregnancy,Flexion contracture at the knee or hip joint > 10°,Varus or valgus deformity at the knee > 10°.

### Allocation

Participants will be randomly allocated to either the intervention group (receiving the Myosuit program) or the control group (initially receiving the conventional program) using a block randomization method. After completion of the conventional program, the control group will as yet be enrolled in the Myosuit program (see Fig. 1). Randomization will be stratified based on preferred walking speed as assessed by the 10-Meter Walk Test (2 categories: < 0.6 m/s; ≥ 0.6 m/s). Group allocation will be done using a 1:1 ratio and in blocks with variable block sizes. Randomization will be performed by the primary researcher (LV), who is aware of the method of the group allocation. CastorEDC, a data management system for academic studies (www.castoredc.com), is used for the randomization.

### Blinding

Given the nature of the intervention, blinding of participants or treating physical therapists is not feasible. Because the primary researcher (LV) is responsible for the randomization process, the certification procedure of the Myosuit for home use, and for all measurements, outcome assessment cannot be blinded. The statistical analyses will not be blinded because they have been defined beforehand.

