#### Primary outcome

The primary outcome measure for daily life gait performance is average walking time per day (min). It will be assessed with the Activ8 sensor (Activ8 Basic Activity Tracker, Activ8, Valkenswaard, The Netherlands), a single-unit activity monitor based on triaxial accelerometry [29]. The Activ8 will be placed on the participants’ right upper leg and measures lying, sitting, standing, walking, running, and cycling activities. Data sampling frequency is 50 Hz. The output provides information on the duration of specific activities within 1 min. The Activ8 has been validated in healthy individuals [29] and post-stroke patients [30] to assess the above-mentioned activities during daily life. Participants will wear the Activ8 continuously for seven consecutive days, 24 h a day. Baseline data (T0) will be averaged over a 7-day period to calculate the mean total walking time per day. During the 6-week home period, data from T2, T3, and T4 (the first, third, and sixth week of the home period) and data from T7, T8, and T9 (the first, third, and sixth week of the home period) will be averaged across all days (T2–T4; T7–T9) to calculate mean total walking time per day. For the primary analysis, the between-group difference in change of mean walking time per day at T2–T4 versus T0 will be of main interest.

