#### Secondary outcomes

##### Spatiotemporal gait characteristics

Secondary outcome measures of daily life gait performance are walking speed (m/s), step length (m), maximum gait bout length (steps), and double support phase duration (s) assessed with inertial measurement units (IMUs). Two IMUs will be attached to both feet, and one will be positioned at the sacrum for 3 days. A self-developed algorithm comparable to previously published algorithms [31–33] will be used to calculate the various gait parameters. Spatiotemporal gait characteristics will be averaged over a 3-day period to calculate the mean at T0 (baseline). Data from the 6-week home period at T2 and T4 (first and sixth week of the home period) and at T7 and T9 (first and sixth week of the home period) will be averaged across all days (T2 + T4; T7 + T9). The between-group difference in change of spatiotemporal gait characteristics at T2 + T4 versus T0 will be analyzed.

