## Discussion

Ambulation in the home and community setting is limited in many people with iSCI [5]. It has been shown that the Myosuit is feasible to be used for various activities in the home and community setting by people with leg muscle weakness [25], but the effect of the Myosuit to increase ambulation in people with iSCI remains unknown. This RCT investigates the assistive effect of the Myosuit on daily life gait performance in people with iSCI. If the Myosuit proves to be effective in increasing physical activity, it may lead to a less sedentary lifestyle and a reduction of secondary complications after iSCI.

We deliberately chose to use a cross-over design for the control group, as we expect this will improve patient inclusion. It also provides a better opportunity to investigate whether personal characteristics are related to improved daily life gait performance with the Myosuit by combining data from both groups. In addition, during the 6-week home periods, participants purposely receive only general exercise recommendations. Although specific home training recommendations may be more effective to increase physical activity, we are primarily interested in the natural improvement of walking time per day as a result of Myosuit availability. Due to the nature of the intervention and as a consequence of study constraints, it is not feasible to blind participants, physical therapists, or the assessor, which may introduce assessment bias, but the primary outcome measure is based on objective recording of daily life gait performance, a measure insensitive to influence from the assessor. Moreover, all measurement procedures are standardized as much as possible to minimize assessor bias.

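### Predefining the analyses is not a reason to leave them unblinded; an avoidable risk of bias remains, mainly for the four secondary IMU gait outcomes

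*Protocol article*

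**What the plan says.** The Blinding section of the protocol article treats three groups separately. Participants and therapists cannot be blinded because of the nature of the intervention. One researcher randomises, certifies participants for home use and is responsible "for all measurements, outcome assessment cannot be blinded". For the analysis stage the reason is of another kind: "The statistical analyses will not be blinded because they have been defined beforehand".

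Two sensor systems supply outcomes:

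- **Primary outcome.** Of daily walking time the article says "It will be assessed with the Activ8 sensor", and of the device, "The output provides information on the duration of specific activities within 1 min". Home-period values from T2, T3 and T4 are averaged over all days.
- **Secondary outcomes.** Walking speed, step length, maximum gait bout length and double support duration come from IMUs on the feet and sacrum, processed by "A self-developed algorithm comparable to previously published algorithms".

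The Discussion concedes that lack of blinding may introduce assessment bias, and answers that "the primary outcome measure is based on objective recording of daily life gait performance, a measure insensitive to influence from the assessor".

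**The concern.** Prespecification and masking protect against different things. A prespecified ANCOVA with the baseline value as covariate stops the analyst from choosing a favourable model. It does not stop someone who knows the arm from making, revising or accepting processing decisions that determine the numbers entering that model. Having the first is therefore no argument for giving up the second.

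In this trial participants, therapists and the assessor are all unblinded, and one person both allocates and measures. Masked processing and analysis is one of the few protections still available, and the article gives it up for a reason that does not bear on it. At stake is the credibility of the between-group comparisons, above all those that depend on code written by the study team.

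**Working it through.** **Step 1: set each blinding decision beside its reason (Blinding; Discussion).**

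| Who is unblinded | Reason given | Kind of reason |
|---|---|---|
| Participants, therapists | Nature of the intervention | Feasibility |
| Outcome assessor | One researcher does randomisation, certification and measurement | Staffing |
| Statistical analyses | They are predefined | Neither |

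The Discussion repeats the infeasibility for the first two rows and does not mention analysts. So the documents state no obstacle to coded arms at the analysis stage.

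**Step 2: what is in fact predefined (Statistical methods; Primary outcome; Secondary outcomes).** The article fixes intention-to-treat, listwise deletion with last observation carried forward as sensitivity analysis, the averaging windows, and ANCOVA on the T0 value. These govern the model and the summary. None governs how an IMU signal becomes a step, a bout or a double support phase.

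**Step 3: which outcomes depend on the in-house algorithm.** The secondary ANCOVAs cover preferred speed, maximum speed, 6MWT and SCI-FAP (4 outcomes) and the IMU measures (4 outcomes). That is 4 + 4 = 8, so 4/8, or half, depend on it. The four clinic tests do not. Their exposure arises when the unblinded researcher takes the measurement, and masked analysis cannot repair that.

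**Step 4: the primary outcome.** The Activ8 is a named monitor, with validation cited in healthy people and after stroke. Its own output already gives activity durations, and the article states how days are averaged. No in-house algorithm is mentioned. The room for arm-aware judgement is therefore smaller, though knowledge of the arm is not removed.

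**Step 5: can the size be computed?** The plan's own figures reproduce:

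- Target: 500 steps × (1.07 s / 2) = 267.5 s = 4.46 min/day, stated as 4.5.
- Sample size: 2 × (1.960 + 1.282)² × (400/500)² = 13.45, so 14 per group, as stated.

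The sample size is not in dispute. No figure in the documents measures processing bias, and no SD is given for any IMU outcome, so where the risk chiefly lies nothing can be calculated. For the primary outcome only a sensitivity illustration is possible. The SD is 400 × 1.07 / 120 = 3.57 min/day. With 14 per group, no true effect and a two-sided 5% t-test, an **assumed** shift between arms gives:

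| Assumed shift (min/day) | Shift / 3.57 | Shift / 4.46 | Rejection rate |
|---|---|---|---|
| 0.25 | 0.07 | 6% | 5.4% |
| 0.5 | 0.14 | 11% | 6.5% |
| 1.0 | 0.28 | 22% | 11.0% |
| 1.5 | 0.42 | 34% | 18.8% |

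The shifts are not from the documents, and no route is shown by which averaging Activ8 output would produce one. The table says how sensitive the test would be, not what to expect.

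**Step 6: would masking work here?** Table 1 shows that T7 to T9 exist only for controls. If all files were batched and linked by participant, anyone with T7 to T9 files would be identified as a control. Masking therefore has to be confined to T0 to T4, the data used in the between-group comparisons. T0 recordings also precede any suit use, so an algorithm settled on T0 data alone would be untested on suit walking.

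**The case against.** The strongest reply is that the choice is openly disclosed, the primary model and averaging rule are stated, and an algorithm applied identically to both arms need not favour either. That stands, and it is why this is a risk and not a finding of bias. It does not rescue the stated reason, which no separate SAP could make valid.

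A reader might infer more than the documents support:

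- **That the in-house algorithm touches the outcome called objective.** It does not. The algorithm serves only the secondary IMU measures, and the Discussion makes the objectivity claim only for the primary outcome. That claim concerns the assessor and says nothing about analysts.
- **That data are cleaned at discretion.** No section describes this or says who processes the sensor files. Valid-day and non-wear rules are commonly left to a full protocol or SAP, so their absence from an article is not a fault.
- **That the open predictor list in the secondary regression belongs to this point.** That model pools Myosuit home periods from both groups and contains no arm contrast, so masking the arm cannot protect the choice of predictors.

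It can also be said that masking is not free. Someone other than the primary researcher must recode files and hold the key, and 23 of 34 participants were already included when the article was written. The first is true but small. The second matters little, because the proposed steps concern processing and analysis and leave recruitment and measurement as they are.

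**Conclusion.** The point holds in a limited form. The justification in the Blinding section is a non sequitur, and it gives up a protection that the documents do not show to be impracticable. The consequence is an avoidable risk of bias, chiefly for the four IMU outcomes (half of the eight secondary ANCOVA outcomes), and to a smaller degree for Activ8 walking time.

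The documents do not support saying that bias has entered or giving it a size. The illustrative rejection rates rest wholly on assumed shifts and should not be quoted as an estimate. The conclusion assumes only that IMU processing involves some choices that could still be made or revised after post-randomisation data are seen. If the full protocol or SAP already locks the algorithm, the remaining risk is smaller, but the stated reason would still need correcting.

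**What to change.** 1. Delete the sentence that offers predefinition as the reason for unblinded analysis. If masking is declined, give a real reason and list it as a limitation.
2. Lock and record the IMU algorithm version before any post-randomisation data are compared by arm. Because T0 contains no suit walking, any check on home-period recordings should be made on coded files without an arm comparison.
3. Process T0 to T4 sensor files under pseudonymous codes, separately from the control-only T7 to T9 files. The codes should be new: study numbers that follow the order of inclusion could be recognised by the researcher who randomised.
4. Run the primary and secondary between-group ANCOVAs with arms labelled A and B. An existing team member other than the primary researcher holds the key and reveals it only after outputs are locked.

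The predictor regression lies outside this change. The cost is wording in the analysis and data-handling documents, some recoding work and a small task for a second team member. Masking will be incomplete where the signal itself reveals suit use, and it does nothing for the clinic tests taken by the unblinded researcher.
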